## Methods

### Study population

The study is conducted among male and female adult patients with diagnosed primary colon cancer T1-4aN0-2bM0-1b and clinical indications for elective colonic resection. All patients should sign an informed consent, meet inclusion criteria, and have no exclusion criteria.

### Eligibility criteria

#### Inclusion criteria

Pathologically confirmed adenocarcinoma of colon (caecum, ascending colon, hepatic flexure, transverse colon, splenic flexure, descending colon, sigmoid);TNM – T1-4aN0-2bM0-1b;clinical indications to colonic resection;

ECOG – 0–2;
signed informed consent.

#### Exclusion criteria

Medical or psychiatric reasons interfering with patient’s decision to participate in the study;pregnancy or breastfeeding;age less than 18 years;medical conditions contraindicating elective surgical procedure;acute bowel obstruction, bleeding, perforation, or other tumor complications affecting urgency of surgical procedure;peritoneal carcinomatosis;invasion of adjacent organs according to preoperative imaging done up to 30 days prior to surgery;hypersensitivity to indocyanine green, sodium iodide or iodine;hyperthyroidism or autonomic thyroid adenomas;kidney failure of any etiology;hepatic failure of any etiology;poorly tolerated indocyanine injection in the past.

### Quality control

#### Quality control of surgical procedures and ICG lymphatic mapping

To provide routine quality control and ensure possibility of intraoperative data assessment surgical procedures are recorded, and recordings are stored to ensure their availability for revision during data monitoring and in cases of adverse events (Fig. 2). Also, all fresh specimens are photographed after marking of lymph node groups and margins of ICG spread.

#### Morphological assessment

Groups of lymph nodes and margins of indocyanine lymphatic spread are marked on non-fixed specimen by a member of a surgical team taking part in the procedure and determined by surgeon in charge of clinical case. Lymph nodes are marked according to Japanese classification^[15]^ depending on performed extent of colonic resection and lymphadenectomy (Fig. 3).

Specimen assessment is performed according to principles, described by N. West *et al*^[17,18]^, protocol of pathology assessment is described in Appendix S2 http://links.lww.com/ISJP/A8 section.

### Patient treatment

#### Preoperative care

Preoperative investigations and treatment of co-morbidities are conducted according to center’s guidelines and protocols. Preoperative staging is to include, but not to be limited to colonoscopy with biopsy, IV contrast CT chest and abdomen (or abdominal MRI if CT is contraindicated), histological confirmation of cancer and cancer embryonic antigen level. In cases of M+, treatment plan of metastases is to be formulated and documented before enrollment. Results of investigations, fitness for surgery and the fact of meeting or not meeting the eligibility criteria are documented in case report form.

In cases of female patients who are not in menopause (having periods now or in cases when the last period was less than 2 years before enrollment), a pregnancy test is performed, and its results are recorded.

#### Patient enrollment

Patients are enrolled by investigating physician. The study in general and the intervention itself together with information about indocyanine green and associated risk are discussed with the patient, and time and opportunity are provided to allow the patient to familiarize with the informed consent. Should any questions arise, they are answered by investigating physician, and enough time for decision making is provided to the patient. After informed consent is signed, patient is considered as enrolled into the trial.

Patients with signed informed consent, meeting all inclusion criteria and having no exclusion criteria are assigned to elective colonic resection with intraoperative ICG lymphatic mapping. Surgeon in charge decides on extent of colonic resection and planned approach.

Data regarding patients’ demographics, tumor’s TNM, size, and location as well as planned surgery are recorded in case report form.

#### Surgical procedure

Surgical operation is performed under general anesthesia with or without thoracic epidural block. Lymphatic mapping procedure and fluorescence assessment are described in Appendix S1 http://links.lww.com/ISJP/A7 section. Date of surgery, data on operating surgeon and surgeon performing ICG mapping, and technical defects of ICG injection, including spillage, are recorded. Presence and time until pericolic fluorescence, fluorescence along feeding vessels, and aberrant fluorescence (if any is present), influence of ICG spread on resection margins, and intraoperative complications are traced and recorded in case report forms as well.

#### Pathology report

Pathological examination includes macroscopic and microscopic assessments, described in Appendix S2 http://links.lww.com/ISJP/A8 section. During pathological examination each lymph node is assessed both for presence of metastases and for its exact location in relation to primary tumor and margins of indocyanine distribution.

#### Postoperative care

Postoperative care is provided according to local guidelines. Adverse events are registered according to Clavien–Dindo classification. Treatment for complications follows local standards. Data on beginning, duration and treatment for complications is documented in patients’ case report form. Time frame for recording of adverse events is 30 days after surgery. No follow-up is done after this point.

#### Efficacy and safety

Efficacy and safety of surgical procedures are assessed based on pathology reports and postoperative morbidity and mortality. Safety analysis is performed every 25 enrolled patients. Should deviation of morbidity and mortality or frequency of adverse events exceed 30% in intervention group compared to average center statistics for colonic resections, principal investigator and research physician will consider trial discontinuation.

Surgery risks, preferable approach and conversion decisions are surgeon’s responsibility.

In current study adverse event is any unfavorable or unwanted deviation including laboratory tests or condition not necessarily associated with surgery; any change from postoperative state of patient, including exacerbation of co-morbidities. Serious adverse event – any adverse event resulting in death, life-threatening condition, requiring hospital admission or prolongation of in-hospital treatment, permanent disability, or incapacity. Adverse events classification is performed in accordance with CTCAE v. 5.0 terminology.

### Data collection, management and analysis

#### Data quality

Data is entered to electronic CRF (eCRF) by data manager and verified by research physician after enrollment of every 25 patients. Details of surgical procedures are verified by comparing entered data to procedure recordings. All patients’ data is monitored to achieve verification of 100% of data.

#### Collection, storage and sharing of data

Clinical data (demographics, diagnosis, investigations, surgery data, pathology, lab results, etc.) is entered to eCRF basing on primary medical documentation (patient files, outpatient files, investigation reports, laboratory reports, operation notes etc.).

Data in eCRF is entered via google forms and stored under unique identification numbers. Access to data tables is password protected. Only principal investigator and research physician have access to data tables, which are stored for at least 15 years after the end of the study.

After verification data is exported for statistical analysis using SPSS software.

Publications of protocol, first safety report and results in relevant journals are planned. The data will also be shared among specialists via presentations on conferences.

### Sample size calculation and statistical analysis

As the study is aimed to access if ICG mapping can be used to reliably define resection margins in colon cancer surgery, a case of affected lymph nodes only within fluorescence margins was regarded as a true positive case, no fluorescence in pN0 – true negative, pN+ because of metastatic lymph nodes outside fluorescence zone – false negative, pN0 despite presence of fluorescence – false positive.

Sample size of 101 patients was calculated using Buderer method^[19]^ with a confidence level (1 – *α*) of 0.95 as a minimum of cases required to test accuracy of lCG lymphatic mapping for estimated sensitivity of 0.99 and precision (margin of error) of 0.03. This resulted in sensitivity threshold of 0.96. The calculation was performed for minimum acceptable kappa (k0) of 0.6, expected kappa (k1) 0.9. The resultant estimated power (1 – *β*) is 0.96. The average of pN+ cases in our center (42%) was used as prevalence – proportion of outcome (p).

For statistical analysis of primary endpoint, sensitivity will be calculated according to standard formula (number of true positive cases divided by sum of true positive and false negative cases) and its meaning will be compared to the estimated 0.99 ± 0.03. For analytical purposes other measures of accuracy will be calculated as well.

“Intent-to-treat” analysis will be performed, thus once enrolled patients are to be analyzed, irrespective of received treatment. To focus on specificities ICG spread regardless of influence of patients with treatment deviations and those with unsuccessful ICG injection, “per-protocol” analysis will be performed as well.

For secondary endpoints type of analysis will depend on nature of the data. Descriptive statistics will be used to depict feasibility of ICG lymphatic mapping, incidence of adverse events, incidence of lymph node metastases outside conventional resection margins and proportion of operations which extent is affected by ICG lymphatic mapping. Lymph node metastases pattern will be assessed as calculation of frequency of affected nodes related to number of studied nodes in each group. Parametric and non-parametric criteria will be used to compare mean values and contingency tables.

In cases of missing data, should more than 10% of data be missing, the variable will be deleted, because estimates are likely to be biased^[20]^. In other situations multiple imputations will be used.

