**Methods::**

This is a single center interventional phase II trial with single group assignment aiming to determine if ICG lymphatic mapping sensitivity is sufficient to guide resection margins selection in colon cancer surgery. The trial’s primary endpoint is proportion of pN+ patients in which affected lymph nodes are detected only within margins of ICG spread. Sample size of 101 patients was calculated using Buderer method ^[19]^ with a confidence level (1 − *α*) of 0.95 as a minimum of cases required to test accuracy of lCG lymphatic mapping for estimated sensitivity of 0.99 and precision of 0.03. The average of pN+ cases in our center (42%) was used as prevalence. Secondary endpoints are incidence of adverse events related to ICG lymphatic mapping, feasibility of ICG lymphatic mapping for colon cancer, incidence of lymph node metastases outside conventional resection margins (10 cm), colon cancer lymphatic spread patterns, proportion of operations which extent is affected by ICG lymphatic mapping. The trial is conducted among female or male patients, 18 years or older, with signed informed consent, and diagnosed primary colon cancer. Inclusion criteria include pathologically confirmed adenocarcinoma of the colon, T1-4aN0-2bM0-1b, clinical indications to colonic resection, ECOG – 0–2. Exclusion criteria consist of acute bowel obstruction, bleeding or perforation, adjacent organ invasion or peritoneal carcinomatosis, and contraindications to ICG administration. Eligible patients are allocated for colonic resection with intraoperative ICG mapping. During pathological examination, lymph nodes are assessed for presence of metastases and location in relation to tumor and fluorescence margins. The study began on 26 July 2022 and is conducted in and financed by N.N. Petrov NMRC of Oncology in Saint Petersburg, Russia, it is conducted in.

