#### Endpoints

Primary endpoint
Proportion of pN+ patients in which affected lymph nodes are detected only within margins of ICG distribution (number of patients with affected lymph nodes located within ICG distribution margins divided by the number of all patients with pN+).

Secondary endpoints
Incidence of adverse events related to ICG lymphatic mapping (time frame: 30 days after operation);feasibility of ICG lymphatic mapping for colon cancer (proportion of cases with ICG spillage affecting interpretation);incidence of lymph node metastases outside conventional resection margins – 10 cm (proportion of patients with aberrant lymphatics leading to affected lymph nodes);colon cancer lymphatic spread pattern (descriptive data on incidence of D1, D2 and D3 lymphatic collector metastases and frequencies of D1 collector metastases depending on distance from primary tumor);proportion of operations which extent is effected by ICG lymphatic mapping (number of patients with change of operation plan due to mapping results divided by the number of patients).

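### The stated 95% precision of 0.03 for sensitivity is a normal-approximation half-width that about 42 pN+ patients do not deliver; exact half-widths are about 0.04 to 0.06, with lower arms of about 0.08 to 0.10

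*Protocol article*

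**What the plan says.** In the Protocol article, section Sample size calculation and statistical analysis, the plan states: "Sample size of 101 patients was calculated using Buderer method". The inputs are a 95% confidence level, "for estimated sensitivity of 0.99 and precision (margin of error) of 0.03", and a pN+ prevalence taken from the centre's own experience: "The average of pN+ cases in our center (42%) was used as prevalence". The Abstract (Methods) repeats the claim: "for estimated sensitivity of 0.99 and precision of 0.03".

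The same section carries the margin into the analysis. It says "This resulted in sensitivity threshold of 0.96", and of the observed sensitivity that "its meaning will be compared to the estimated 0.99 ± 0.03". The Endpoints section makes pN+ patients the denominator of the primary endpoint, so the precision depends on about 42 patients and not on all 101.

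The sample size section also prints kappa values of 0.6 and 0.9 and a power of 0.96. The margin of 0.03 is its only statement of how precisely sensitivity will be estimated.

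**The concern.** A symmetric normal interval for a proportion needs a reasonable expected number of both successes and failures. Here the failures are false negatives, and fewer than one is expected. In that range the binomial distribution is strongly skewed, and the Wald half-width at the assumed value says little about the interval the trial will obtain. A sign of this is visible in the text: 0.99 plus 0.03 is 1.02, which is not a possible sensitivity.

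What is at stake is how a good result will be read. The Abstract (Results) and Table 2 treat an observed sensitivity around 96% or higher as support for relying on the mapping. The Objectives and study hypothesis section links the absence of metastases beyond the fluorescent zone to smaller resections. A reader told that sensitivity is known to within 3 points would take a clean result as stronger evidence than about 42 pN+ patients can give.

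**Working it through.** **Inputs** (all from the sample size section): expected sensitivity Se = 0.99, margin d = 0.03, confidence 0.95, prevalence 0.42, N = 101. Sidedness is not stated. The two-sided z = 1.96 reproduces N, whereas the one-sided z would give 71.

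**1. The plan's own figure.** Buderer's formula is n(pN+) = z² × Se × (1 − Se) / d².
- 1.96² × 0.99 × 0.01 / 0.03² = 42.26 pN+ patients.
- 42.26 / 0.42 = 100.6, rounded up to 101.

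The figure reproduces, so 0.03 is the Wald half-width evaluated at 0.99.

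**2. Expected counts.**
- 101 × 0.42 = 42.4 pN+ patients.
- 42 × 0.01 = 0.42 expected false negatives.
- At a true sensitivity of 0.99, P(0 false negatives) = 0.99^42 = 0.656.
- P(1) = 42 × 0.01 × 0.99^41 = 0.278.
- Together these two results have probability 0.934.

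**3. Interval for each likely result at 42 pN+ patients.** For 42/42 the exact lower limit is 0.025^(1/42) = 0.916. For 41/42 the lower limit solves p^42 + 42 × p^41 × (1 − p) = 0.025, giving 0.874, and the upper limit is 0.975^(1/42) = 0.999.

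| Result | Estimate | Wald half-width | Exact 95% CI | Exact half-width | Estimate minus lower limit |
|---|---|---|---|---|---|
| 42/42 | 1.000 | 0.000 | 0.916–1.000 | 0.042 | 0.084 |
| 41/42 | 0.976 | 0.046 | 0.874–0.999 | 0.063 | 0.102 |
| 40/42 | 0.952 | 0.064 | 0.838–0.994 | 0.078 | 0.114 |

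None of these gives 0.03 by either method. For the two likely results:
- Half-width: 0.042 / 0.03 = 1.4 and 0.063 / 0.03 = 2.1 times the stated margin.
- Lower arm: 0.084 / 0.03 = 2.8 and 0.102 / 0.03 = 3.4 times the stated margin. Averaged over all results at a true sensitivity of 0.99, the lower arm is 0.091.

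**4. Dependence on the interval method.** The protocol names no interval for the analysis, so the choice is an assumption. Lower arms for 0 and 1 false negatives with 42 pN+ patients:

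| Method | 0 false negatives | 1 false negative |
|---|---|---|
| Clopper-Pearson | 0.084 | 0.102 |
| Wilson | 0.084 | 0.099 |
| Jeffreys | 0.058 | 0.082 |
| Agresti-Coull | 0.100 | 0.111 |
| One-sided 95% exact | 0.069 | 0.084 |

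**5. Dependence on the pN+ count.** With 101 patients at 42%, the 95% range for the pN+ count is 33 to 52. At 52 with no false negatives the exact lower limit is 0.025^(1/52) = 0.932, still about 0.07 below the estimate. A lower arm of 0.03 with no false negatives would need 122 pN+ patients, about 291 in all (122 / 0.42).

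**The case against.** The strongest reply is that 0.03 is a planning quantity and not a promise about the width of the final interval. Read as a statement about sampling error, it nearly holds. If the true sensitivity is 0.99, results of 42/42 and 41/42 give 1.000 and 0.976, both within 0.03 of the truth, with probability 0.934. Averaged over the random pN+ count the figure is 0.938. That is correct, and it rules out saying that the estimate will usually be off by more than 3 points. But it is a property at one assumed true value. It does not say which true values the data leave open, which is what a 95% margin of error is normally taken to mean.

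A second reply is that the ratio of three compares a half-width with the long arm of an asymmetric interval. This stands: like for like, the interval is 1.4 to 2.1 times wider. The factor of three applies only to the lower arm, although that is the side that matters for missed metastases.

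Third, Clopper-Pearson is conservative, with actual coverage of 0.991 at a sensitivity of 0.99 and 42 patients. Jeffreys gives shorter lower arms, but these are still about twice 0.03 or more.

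A reader might also infer that the trial will report a Wald interval, so that 42/42 would be published as 100% with zero uncertainty. The document does not say so. Coverage of a nominal 95% Wald interval would be only 34% at a sensitivity of 0.99, but that figure matters only if such an interval were used. The choice of reporting interval may properly sit in an analysis plan that is not shown. An exact interval there would still leave the published 0.03 unsupported.

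**Conclusion.** The point holds as a fault in the stated precision. The sample size arithmetic is correct; the Wald approximation behind the margin is not valid with 0.42 expected false negatives. At about 42 pN+ patients, with 0 or 1 false negatives, the exact 95% half-width is about 0.04 to 0.06 and the lower limit lies about 0.08 to 0.10 below the estimate (about 0.06 to 0.08 by Jeffreys). The best possible result, 42/42, leaves a sensitivity as low as 0.916 open, meaning missed metastases in up to about 8% of pN+ patients.

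These figures assume a two-sided 95% interval, the protocol's prevalence of 42% and its expected sensitivity of 0.99. That no standard interval delivers 0.03 does not depend on the method chosen.

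The conclusion does not extend to a claim that 101 is miscalculated or that a Wald interval is planned for reporting. Where the 0.96 cut-off should lie, and whether the kappa and power figures are sound, are separate questions.

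**What to change.** Keep N = 101. In the Abstract (Methods) and in the sample size section, replace the precision of 0.03 with what the design delivers. Suggested wording: *With about 42 pN+ patients, the exact 95% confidence interval for sensitivity would be 0.916 to 1.000 with no false negatives and 0.874 to 0.999 with one.*

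Do not present 0.99 ± 0.03 as a 95% interval. State, here or in the analysis plan, that the primary sensitivity will be reported with a Clopper-Pearson or Wilson 95% interval on the observed number of pN+ patients.

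This changes wording only and needs no extra patients, procedures or data. The cost is that the stated precision looks less favourable.

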## Introduction

### Background and rational

Navigational surgery including mapping and tailoring of resection margins can be a solution to the major problem of colon cancer surgery: finding “the least possible not to compromise oncological safety” resection clearance for each patient. Mentioned concept has already been discussed^[1,2]^. But although the idea that all patients are different and therefore require different approaches sounds reasonable, this notion has not met sufficient response because yet there is no tool with proven effectiveness to implement it.

However, there is a lot of evidence on ICG fluorescent imaging for visualization of locoregional lymphatic paths of colonic lesions^[2,3]^, which can guide tailoring. ICG was firstly implemented as a sentinel lymph node detection (SLND) tool but was found to lack accuracy and standardization. Ankersmit *et al* analyzed 8 studies describing 227 SLN procedures in a meta-analysis in 2019 and observed low pooled sensitivity of 63%, negative predictive value 81% and detection rate of 94%^[4]^. The same year Villegas-Tovar *et al* reported similar findings in another meta-analysis of ICG SLND accuracy for colon cancer: they calculated detection rate of 91% (80–98%), sensitivity of 64.3% (51–76%), and specificity of 65% (36–85%) – and concluded that overall ICG performance for detection of lymph node metastases is poor^[5]^. So, it was shown that ICG does help to visualize lymphatics, but it does not work for SLND in colon cancer.

Moreover, assessment of fluorescence and fluorescent lymph node harvest are affected by multiple factors. In particular, 2023 systematic review and meta-analysis of 58 prospective designed studies by Lucas *et al* showed that injection time had a significant impact on aberrant drainage detection favoring preoperative tracer injection^[6]^. The same year Kinoshita *et al* in their series of 56 cases observed both cases with metastatic lymph nodes only in the area along the ICG-stained vascular pedicles and lymph node metastasis in areas along the ICG-unstained vascular pedicles^[7]^.

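### The stated power of 0.96 is that of a two-rater kappa test, not of the sensitivity criterion, and the kappa of 0.9 it assumes does not fit the trial's own premise about ICG spread

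*Protocol article*

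**What the plan says.** In *Sample size calculation and statistical analysis* the Buderer calculation is done "with a confidence level (1 – *α*) of 0.95 as a minimum of cases required", for an "estimated sensitivity of 0.99 and precision (margin of error) of 0.03". The centre's pN+ rate of 42% serves as prevalence. The text continues "This resulted in sensitivity threshold of 0.96". It then states: "The calculation was performed for minimum acceptable kappa (k0) of 0.6, expected kappa (k1) 0.9. The resultant estimated power", reported as 0.96.

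The primary analysis in the same section is true positives divided by true positives plus false negatives, compared with 0.99 ± 0.03. Table 2 sets the success criterion at an observed sensitivity of 96% or higher.

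The section also defines a full 2×2 table. A pN0 patient without fluorescence is a true negative; the remaining cell is "pN0 despite presence of fluorescence – false positive". It adds: "For analytical purposes other measures of accuracy will be calculated as well".

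*Objectives and study hypothesis* assumes that the dye fills the entire regional lymphatic collector, including all affected nodes.

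**The concern.** A reader will take 0.96 as the power of the primary analysis. The section offers it as a product of the sample-size calculation, and *Trial design* says that the risk of a type II error was considered. But a precision calculation yields no power, and kappa appears in no aim, endpoint or described analysis. If the figure comes from an agreement test on all 101 patients, it says nothing about a proportion estimated in the roughly 42 who are pN+.

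The second issue is the kappa itself. If ICG normally lights up the regional collector whether or not nodes are affected, a fluorescing pN0 patient is the technique working as intended. The 2×2 table scores that patient as an error. Agreement and specificity built on this table could then be very low for reasons unrelated to whether the ICG zone contains the metastases.

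**Working it through.** **1. The sample size.** Inputs from the sample-size section: sensitivity 0.99, half-width 0.03, 95% confidence, prevalence 0.42.

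- pN+ needed: 1.96² × 0.99 × 0.01 / 0.03² = 42.26
- Total: 42.26 / 0.42 = 100.6, rounded up to 101

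This reproduces N = 101. Neither kappa nor power enters. The threshold of 0.96 is 0.99 − 0.03, and its match with the power of 0.96 is a coincidence.

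**2. The power of 0.96.** Two-rater binary kappa goodness-of-fit test, 1 df, two-sided 5% (the article does not state sidedness). With common proportion p = 0.42, the probabilities of both positive, discordant and both negative are p² + κp(1−p), 2p(1−p)(1−κ) and (1−p)² + κp(1−p).

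| κ | both positive | discordant | both negative |
|---|---|---|---|
| 0.6 | 0.3226 | 0.1949 | 0.4826 |
| 0.9 | 0.3956 | 0.0487 | 0.5556 |

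- Sum of (difference)² / null probability: 0.0166 + 0.1096 + 0.0111 = 0.1372
- Non-centrality for n = 101: 13.86. Power: Φ(√13.86 − 1.96) = Φ(1.763) = 0.961
- Same test on 42 patients: non-centrality 5.76, power 0.67

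The stated 0.96 is therefore reproduced by a kappa test on all 101 patients.

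**3. The criterion actually planned.** With 42 pN+ patients, 40/42 = 0.952 fails and 41/42 = 0.976 passes.

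- True sensitivity 0.99: 0.99⁴² + 42 × 0.01 × 0.99⁴¹ = 0.656 + 0.278 = 0.934
- True sensitivity 0.96: 0.96⁴² + 42 × 0.04 × 0.96⁴¹ = 0.180 + 0.315 = 0.495

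With 43 pN+ patients these are 0.931 and 0.483. Averaged over a Binomial(101, 0.42) number of pN+ patients, they are 0.938 and 0.514.

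**4. Kappa under the article's 2×2 definitions.** Take sensitivity 0.99 and prevalence 0.42, so TP = 0.4158 and FN = 0.0042. Let f be the proportion of pN0 patients who fluoresce, so FP = 0.58f and TN = 0.58(1 − f). The article gives no expected f. As an assumption I use the detection rates it cites from two sentinel-node meta-analyses: 94%, and 91% with interval 80–98%.

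| f | observed agreement | chance agreement | kappa |
|---|---|---|---|
| 0.94 | 0.4506 | 0.4262 | 0.04 |
| 0.91 | 0.4680 | 0.4290 | 0.07 |
| 0.80 | 0.5318 | 0.4392 | 0.17 |

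Kappa of 0.9 requires specificity of about 0.92: observed agreement 0.9506, chance agreement 0.5062, kappa 0.4443 / 0.4938 = 0.90. That means fluorescence in no more than about 8% of pN0 patients. The specificity of 65% cited from one of the meta-analyses gives kappa 0.60, the stated minimum.

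**The case against.** **Little depends on the sentence.** N, endpoint, threshold and decision rule all survive its deletion, and 0.93–0.94 is only two to three points below 0.96. This stands and limits the weight of the point. It does not make the figure right: it comes from another hypothesis and other patients, and it hides that the rule passes about half the time at a true sensitivity of 0.96.

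**The fluorescence rates are borrowed.** They come from sentinel-node work, an approach the Introduction itself rejects for colon cancer, and are applied here to pN0 patients. This also stands, so the kappa range is conditional. The premise in *Objectives and study hypothesis* nevertheless points to frequent fluorescence.

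Stronger readings that a reader might infer are not supported:

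- *The definitions make kappa 0.9 impossible.* They do not. At specificity 1, kappa would be 0.99. The conflict needs the added premise that most pN0 patients fluoresce.
- *The trial has no power.* A one-sided exact 5% test against 0.96 could not reject with 42 patients (42/42 gives p = 0.18), but the article plans no such test. Its rule uses the observed proportion.
- *Kappa will never be analysed.* The full protocol and the SAP are not shown. One can say only that the article describes no kappa analysis.
- *All other accuracy measures are worthless.* Negative predictive value stays at 0.89–0.93 for f of 0.94–0.91 (0.0348/0.0390 and 0.0522/0.0564), and success depends on sensitivity alone.

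**Conclusion.** The concern holds in limited form. The power of 0.96 is wrong as attached: it is that of a two-sided 5% two-rater kappa test on 101 patients, while the planned primary analysis is a sensitivity in about 42. For that analysis the honest figures are about 0.93 at a true 0.99 and about 0.50 at a true 0.96 (0.94 and 0.51 averaged over the random pN+ count), assuming 42% prevalence and the observed-proportion rule of Table 2.

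The expected kappa of 0.9 is incompatible with the premise that ICG fills the regional collector once fluorescing pN0 patients count as false positives. The size, kappa about 0.04–0.17, rests on the assumed 80–94% fluorescence in pN0 and on sensitivity 0.99. The sample size is not in error.

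**What to change.** Delete the kappa sentence and the power of 0.96. Replace them with wording such as: *With about 42 pN+ patients, the criterion of an observed sensitivity of at least 0.96 requires 41 of 42. The probability of meeting it is about 0.93 if true sensitivity is 0.99 and about 0.50 if it is 0.96 (0.94 and 0.51 averaged over the number of pN+ patients).* Leave N = 101 as it is.

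Do not treat fluorescence in a pN0 patient as a mapping error. Either drop the true-negative and false-positive labels, or report specificity, positive predictive value and overall accuracy only with a note that they do not measure whether the ICG zone contains the metastases. Add the proportion of all patients with visible fluorescence; *Surgical procedure* already has its presence recorded.

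The cost is wording only: no extra patients or data. The price is a less favourable stated figure.
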